#### Statistical Analysis

Qualitative and quantitative descriptive data analyses will be conducted according to the research questions. Confidence intervals will be determined for both the frequency of use of the main modules and the completion rate of the intervention until t_1_. We will investigate change in the 30-days prevalence of alcohol and/or cannabis and on the GAD-7 and the PHQ-9 scores using linear mixed effect models.

#### Ethical Considerations

Before the trial, ethical approval was obtained from the ethics board of the Catholic University of Applied Sciences North Rhine-Westphalia. All data processing will be conducted according to the current Data Protection Act, and the data protection officer of the above-named university monitors issues regarding data protection. All study participants and app users will receive detailed information on study goals, analyses, and data reporting. They will give their informed consent and accept the terms of use of the application before participation in the study. All data are saved on a protected server.

Serious Adverse Events (SAE; pregnancy, diagnosed addiction, sickness, heart or liver disease) are considered to be theoretical and are not expected. However, these events are registered using a medical questionnaire, which provides feedback on health-related contraindications regarding any further substance use. This information is systematically documented throughout the assessments.

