##### Referral Pathways

Participants with high scores on the AUDIT or the CUDIT-R that indicate an alcohol or cannabis use dependency, respectively, will receive personalized feedback that suggests and encourages to seek help, provides an example for a counseling center and, in the case of high alcohol use, the warning to “not stop consumption without professional help as it could lead to physical harm or danger (e.g., cramping).” Furthermore, the intervention provides information on addiction counseling centers in general and highlights reasons to seek support based on the criteria of ICD-10 (54). In a separate module (see Table 1; Figure 6A) a number to call a hotline for immediate assistance in crisis situations, selected counseling centers and a link to a further (German-wide) search list for addiction counseling centers, as well as additional relevant online applications, are provided.

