#### Secondary Outcome

As a secondary outcome, we will assess the initial efficacy of the DHI by the change from baseline in severity of substance use, depressive symptoms, and symptoms of anxiety. Comparing post-intervention to baseline levels, we will quantify

the initial efficacy of intervention using a 30-day prevalence measure in line with the Epidemiological Survey of Substance Abuse (2018),the change in depressive symptoms with the Patient Health Questionnaire [PHQ-9; (57)], andthe change in symptoms of anxiety with the Generalized Anxiety Disorders Scale-7 (GAD-7; 54).

For an overview of all outcomes and associated measures, see Table 2.

**Table 2 T2:** Measures and assessment at points used in the study.

**Construct (Assessment)**	**Baseline (t_**0**_)**	**Follow-up (t_**1**_/t_**2**_/t_**3**_)**	**Sources of translations**
Sociodemographics^a^^,^ ^b^			See note 2
Age	x		
Gender	x		
Home country	x		
Living situation	x		
Residence status	x		
Occupational status (past and present)	x		
Level of education	x		
Family status	x		
Information on children	x		
Religion	x		
Socio-economic status	x		
Additional inclusion criteria			Arabic, English, Farsi, Pashto: own translations
Refugee background	x		
No current psychiatric or psychological treatment for use of alcohol and/or cannabis	x		
Escape-related information			See Note 2
Dates of escapes' beginning^a^^,^ ^b^	x		
Duration of escape^a^^,^ ^b^	x		
Duration of stay in Germany^a^^,^ ^b^	x		
Accompaniment during escape^a^^,^ ^b^	x		
Burdens of missing information on family and friends^b^	x		
Substance use			
Alcohol (AUDIT)	x		Arabic: Almarri et al. (58); Farsi: Noorbakhsh et al. (59); German: Dybek et al. (60); Pashto: own translations
Cannabis (CUDIT-R)	x		Own translations
30-day prevalence	x	x	Own translations
Confidence in change	x	x	Own translations
Medical Questionnaire (pregnancy, serious disease, medication, SUD)	x		Own translations
Depression (PHQ-9)	x	x	German: Gräfe et al. (61); Arabic, Farsi, Pashto: own translation
Anxiety (GAD-7)	x	x	German: Löwe et al. (62); Arabic, Farsi, Pashto: own translation
Smartphone Use	x		own translations
Program Participation Questionnaire^b^		x	own translations

*1*:

a *Standardized measures with the PREPARE and PrevDrop research consortia*;

b *Standardized measures with the the KS-Diagnostik project*;

*^c^see attachments for full questionnaire*.

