#### Assessments

After obtaining informed consent and an eligibility screen on the app usage (minimum of 18 years of age), the baseline-measurement (t_0_) is scheduled. The baseline questionnaires will consist of items relating to sociodemographics, escape related information, a medical questionnaire on pregnancy, serious disease, medication and SUD, depression, anxiety, and smartphone use (see Table 2). Follow-up measurements are scheduled directly after the intervention (t_1_), as well as at 3-months (t_2_), and at 6-months (t_3_) follow-ups. Assessment and intervention take place on the participants' mobile devices and pending assessments will block further use of the app. A schedule of enrollment, intervention and assessment is shown in Figure 8.

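### The protocol says serious adverse events are documented throughout the assessments, but Table 2 schedules the only instrument named for them at baseline alone

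*Protocol article*

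**What the plan says.** Three places in the protocol article bear on this.

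- **Ethical Considerations** gives the list of SAEs and the expectation about them: "Serious Adverse Events (SAE; pregnancy, diagnosed addiction, sickness, heart or liver disease) are considered to be theoretical and are not expected". It then names the instrument: "However, these events are registered using a medical questionnaire, which provides feedback on health-related contraindications regarding any further substance use". On timing it says: "This information is systematically documented throughout the assessments".
- **Table 2** (under Secondary Outcome) has a row that begins "Medical Questionnaire (pregnancy, serious disease, medication, SUD". It carries a mark under baseline and none under the combined follow-up column for t1, t2 and t3.
- **Assessments** includes the instrument in its description of the baseline questionnaires: "a medical questionnaire on pregnancy, serious disease, medication and SUD, depression, anxiety, and smartphone use (see Table 2". On the later time points it says: "Follow-up measurements are scheduled directly after the intervention (t_1_), as well as at 3-months (t_2_), and at 6-months (t_3_) follow-ups".

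The article names no other instrument for SAEs.

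**The concern.** An adverse event in a trial is something that happens after exposure begins. An instrument given once, before the app's modules are opened, can only describe the participant's state at entry. Whether the medical questionnaire is repeated therefore decides whether its answers are safety data or medical history.

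The people who build and run the app are likely to work from the schedule in Table 2, not from a sentence in the ethics section. If they follow the table, two misreadings become possible, depending on how the answers are handled. If the t0 answers are set aside as history, a later report of no SAEs would mean only that participants were not asked by the instrument meant for the purpose. If the t0 answers are counted as SAEs, conditions that came before the intervention would be reported as events under it. Events not asked about during follow-up may also be hard to recover later, since assessment takes place on the participants' own devices.

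**Working it through.** The plan states no figure to reproduce. The check compares the passages and counts time points.

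**1. Is it the same instrument?** The items in the Table 2 row match the SAE list closely: pregnancy with pregnancy, SUD with diagnosed addiction, and serious disease with sickness and heart or liver disease. Medication is the only item in the row without a counterpart in the SAE list. Both places call it a medical questionnaire, and the article names only one. I take them to be the same.

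**2. Is the empty cell an artefact of text extraction?** Probably not, because the table separates the three possible patterns:

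| Pattern in Table 2 | Rows |
|---|---|
| Baseline and follow-up | 30-day prevalence, confidence in change, PHQ-9, GAD-7 |
| Follow-up only | Program Participation Questionnaire |
| Baseline only | AUDIT, CUDIT-R, smartphone use, medical questionnaire, among others |

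The rows just above and just below the medical questionnaire (confidence in change and PHQ-9) both carry follow-up marks.

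**3. How often is the questionnaire given?** There are four time points: t0, t1, t2 and t3.

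| Source | Time points with the SAE instrument | Follow-ups with it |
|---|---|---|
| Table 2 | 1 of 4 (t0) | 0 of 3 |
| Ethical Considerations, read as every assessment | 4 of 4 | 3 of 3 |

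**4. Does the Assessments section settle it?** No. It mentions the questionnaire only at baseline ("a medical questionnaire on pregnancy, serious disease, medication and SUD"), which fits Table 2. But the same sentence lists depression and anxiety at baseline, and Table 2 repeats both at follow-up. The section does not itemise the follow-up content, so its silence is weak support at best. The contradiction rests on Table 2 against Ethical Considerations.

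**5. Could other follow-up measures stand in?** Only in part. The PHQ-9, GAD-7 and 30-day prevalence are collected at t1, t2 and t3. They would show a rise in depressive symptoms, anxiety or substance use. None of them asks about pregnancy, a new diagnosis of addiction, sickness, or heart or liver disease. The article classes them as secondary outcomes, not as SAE reporting.

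**The case against.** The strongest reply is that the SAE text itself promises repeated documentation, so the intent is right and Table 2 may simply lack a mark. Figure 8 (the schedule of enrolment, interventions and assessments) and Appendix 1 are not shown and might settle it. A journal article also condenses a fuller protocol, and details of SAE reporting commonly stand there. The trial is a single-arm feasibility study of an app, and safety is not one of its listed outcomes. All of this stands, and it limits the point to a contradiction. It does not remove the point, because the article states the timing in two places and the two disagree.

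A reader might be tempted to go further in four ways that the documents do not support.

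- **That no harm during or after the intervention can be recorded.** The repeated PHQ-9, GAD-7 and 30-day prevalence would show some kinds of worsening, and the SAE text asserts repeated documentation.
- **That the SAE list is by nature a list of entry conditions.** It includes sickness, and sickness, pregnancy or a new diagnosis can each begin during follow-up. Only the disputed timing would turn the answers into history.
- **That the list leaves out the one harm the app warns of.** Referral Pathways does tell participants with high alcohol use to "not stop consumption without professional help as it could lead to physical harm or danger (e.g., cramping", and the SAE list does not name this. But the full app content is not shown, so it cannot be called the only warning, and such an event might be reported as sickness.
- **That the data safety and monitoring board will receive no post-baseline safety data.** The Data Monitoring section does not describe what the board receives, and that detail may stand in the full protocol.

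**Conclusion.** The concern holds as an internal contradiction. Ethical Considerations says that SAE information is collected throughout the assessments, while Table 2 schedules the only named SAE instrument at 1 of 4 time points. If Table 2 is followed, 0 of 3 follow-ups administer it, and the listed SAEs are recorded only as conditions present before the intervention.

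This rests on two assumptions: that the medical questionnaire in Table 2 is the one named in the SAE text, and that the empty follow-up cell is as printed. Both are well supported by the article. Which of the two statements reflects the study as run cannot be told from the article, so a failure to capture later events is a conditional consequence and not an established fact. No event rate is at issue, since the article plans none.

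**What to change.** Reconcile Table 2 with Ethical Considerations, and make Figure 8 agree if it does not already:

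1. Mark the medical questionnaire in the follow-up column of Table 2, so that it is given at t1, t2 and t3.
2. At those time points, ask about new events since the last assessment, so that a condition already reported at t0 is not counted again.
3. In Ethical Considerations, name the time points at which SAEs are recorded.
4. Report the t0 answers as medical history, separately from events with onset after baseline.

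The cost is small. The instrument exists, and the app already runs questionnaires at all three follow-ups and locks further use while one is due. The downside is a slightly longer follow-up form.

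### Ethical Considerations says event information is documented across the assessments, but Table 2 marks the medical questionnaire that registers events at baseline only

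*Protocol article*

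**What the plan says.** The last paragraph of Ethical Considerations defines the events and states the expectation: "Serious Adverse Events (SAE; pregnancy, diagnosed addiction, sickness, heart or liver disease) are considered to be theoretical and are not expected". It then names the means of capture: "these events are registered using a medical questionnaire, which provides feedback on health-related contraindications regarding any further substance use". It closes with the timing: "This information is systematically documented throughout the assessments".

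Table 2 (under Secondary Outcome) is the article's list of measures by time point. It has one column for baseline (t0) and one for the three follow-ups together (t1/t2/t3). The row "Medical Questionnaire (pregnancy, serious disease, medication, SUD" carries a mark under baseline and none under follow-up.

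The Assessments section describes the baseline questionnaires as including "a medical questionnaire on pregnancy, serious disease, medication and SUD, depression, anxiety, and smartphone use (see Table 2". On the later visits it says: "Follow-up measurements are scheduled directly after the intervention (t_1_), as well as at 3-months (t_2_), and at 6-months (t_3_) follow-ups". It does not list the instruments used at those visits, and it refers to Figure 8 for the schedule.

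**The concern.** The safety paragraph promises documentation over the course of the assessments, and the table of measures schedules the instrument once. Whoever programs the app or the data export from Table 2 will give the questionnaire at t0 and not again.

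The timing matters because the intervention begins only after the baseline assessment (Structure and Content of the Digital Intervention). A pregnancy or disease reported at t0 is a condition the participant already had. It says nothing about what happened during the 4 weeks of app use or up to the 6-month follow-up. The contraindication feedback is attached to the same questionnaire, so under Table 2 it could not be prompted by a condition that arises later. The consortium's monitoring board (Data Monitoring) would receive no post-baseline event information from this instrument.

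**Working it through.** No arithmetic beyond a count applies, and the plan gives no figure to reproduce. The check sets the passages side by side.

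1. **Means of capture.** Ethical Considerations names one instrument for registering events, the medical questionnaire. Elsewhere, the log files (Study Adherence) record frequency and duration of use. The PHQ-9 and GAD-7 measure depressive and anxiety symptoms, not the listed events. The Program Participation Questionnaire is described as measuring feasibility and acceptability. Data Monitoring states that a board exists but describes no data source for it.

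2. **Timing in the safety paragraph.** The closing sentence speaks of the assessments in the plural and of documentation running through them. The plain reading is repeated administration.

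3. **Timing in Table 2.** The medical questionnaire has a mark at t0 and an empty follow-up cell.

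4. **Is the empty cell an artefact of text extraction?** The neighbouring rows suggest not.

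| Table 2 row | t0 | t1/t2/t3 |
|---|---|---|
| 30-day prevalence | x | x |
| "Confidence in change" | x | x |
| Medical Questionnaire | x | – |
| PHQ-9 | x | x |
| GAD-7 | x | x |
| Smartphone use | x | – |
| Program Participation Questionnaire | – | x |

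Four rows are marked in both columns and one at follow-up only. The table does mark repeated measures, and it does not mark this one.

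5. **Does the Assessments text decide the matter?** It does not. It places "a medical questionnaire on pregnancy, serious disease, medication and SUD" at baseline, but the same sentence lists depression and anxiety, which Table 2 repeats at follow-up. Being named at baseline therefore does not imply baseline only. The baseline-only schedule rests on Table 2.

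6. **Count.** Table 2 gives the questionnaire at 1 of 4 time points (t0) and at 0 of 3 follow-ups (t1, t2, t3). The safety paragraph implies administration at the follow-ups as well. Since t0 precedes use of the app, Table 2 leaves this instrument with no observation after exposure begins.

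**The case against.** The strongest reply is that this is one empty table cell against one loosely worded sentence in a condensed article. Figure 8 is the completed schedule figure and was not available in readable form. If it marks the follow-ups, the fault may be no more than a missing mark in Table 2. The closing sentence could also be read loosely, as saying that the information is gathered within the assessment process. Detailed event procedures are commonly left to the full protocol.

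Part of this stands. The article alone does not show which schedule is intended, and a single missing mark is a plausible explanation. The mismatch remains either way: a Figure 8 that marks follow-ups contradicts Table 2, and one that does not contradicts the plain reading of the safety paragraph. A safety statement that needs a loose reading should be reworded.

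Four stronger readings are tempting, and the documents do not support them:

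- *The Assessments section also restricts the questionnaire to baseline.* It does not say so, for the reason given in step 5 of the working.
- *No event after the start of the app can be captured at all.* The text supports this only for the one instrument named. The full protocol may describe another route.
- *The trial would report zero events by construction.* A baseline register would hold conditions already present that match the event list, so it need not be empty. Nothing in the article announces a no-events result.
- *The loss can be expressed as an upper bound on event risk given zero events.* Adverse events are not among the primary or secondary outcomes, and Statistical Analysis plans no safety analysis. Such a bound would answer a question the protocol does not ask.

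**Conclusion.** The point holds as an internal contradiction about when the medical questionnaire is given. The safety paragraph implies repeated documentation, while Table 2 schedules the instrument at 1 of 4 time points and at none of the 3 follow-ups. If Table 2 is followed, the only instrument the article names for registering events records pre-existing conditions. After t0 it can neither register an event nor trigger the contraindication feedback.

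This rests on three things: the plain reading of the closing sentence in Ethical Considerations, the empty cell in Table 2 as extracted (supported by the neighbouring rows), and the intervention starting after baseline. It does not depend on sample size, dropout or any other numerical assumption. The primary feasibility and acceptability outcomes are unaffected. The correction should be made because a stated safety procedure conflicts with the table of measures meant to implement it.

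**What to change.** Reconcile Table 2 with the last paragraph of Ethical Considerations, check both against Figure 8, and state in Assessments which instruments are given at follow-up. There are two consistent ways to do this:

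- **If repeated documentation is intended:** mark the Medical Questionnaire in the t1/t2/t3 column of Table 2, and have the records separate conditions present at baseline from those newly reported at follow-up. The cost is a slightly longer questionnaire at three assessments already scheduled in the app. If the follow-up items are reworded, some new translation is needed for the app's five languages.
- **If baseline-only administration is intended:** delete the closing sentence of the safety paragraph, and state that this instrument yields no post-baseline event data and supports no safety conclusion. The cost is wording only. If the full protocol has another route for capturing events, name it here.

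Which option matches the intended safety procedure is for the sponsor to settle.

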#### Data Monitoring

The PREPARE research consortium (“Prevention and Treatment of Substance Use Disorders in Refugees (PREPARE)” organizes a central data safety and monitoring board. A list of members can be requested at the consortium coordinator [name]. [name] ([contact]).

## Discussion

The present study protocol describes the development and the design of the evaluation study on the “BePrepared App” as a digital health intervention (DHI) for a substance use reduction in young refugees with problematic use of alcohol and/or cannabis. The primary goal of the feasibility trial is to assess the DHI's usability and acceptability among the targeted group. Secondary, we aim to give an indication on its initial efficacy in leading to a substance use reduction. According to our preliminary research and a rapid review by Liem et al. (70), which identified 16 digital mental health technologies for immigrants and refugees, however, none of which targeting substance use prevention or treatment, we believe the “BePrepared App” to be one of the first digital health intervention to deal with the indicated prevention of substance use disorder among refugee populations worldwide and to be scientifically evaluated (71). If successful, this study may contemplate to overcoming care barriers by providing refugee populations with urgently needed access to preventive health care through delivering accessible indicated prevention. As a stand-alone intervention not presenting personalization or face-to-face contact, it may become a significant additional tool within a larger set of interventions (72).

### Implications

This evaluation study allows to draw conclusion about the usability and acceptability of the DHI among young refugees with problematic use of alcohol and/or cannabis. This forms the basis for further research on the efficacy of the DHI. The description of the intervention development and study design allows to replicate the study as well as to retrace where the weaknesses and strengths of the DHI lie.

Under the assumption that the DHI is in fact feasible in terms of being used and accepted by the targeted group, the DHI itself has several strengths. It is independent of location and time, free of costs, and easily accessible. It reduces language barriers, which in turn reduces treatment barriers. It addresses the topic of substance use and substance use prevention with cultural sensitivity and respects the target users' social contextual factors.

